**Knowledge of obstetric danger signs**

Women who mention at least three neonatal danger signs will be considered to have good knowledge whereas those who mentioned less than three of the danger signs will be labelled to have poor knowledge as stated by several studies.

**Perception of pregnancy risk**

Risk perception is operationalized using the adapted Perception of Pregnancy Risk Questionnaire (PPRQ) developed by Heaman & Gupton. Higher scores will indicate higher levels of perceived risk.

**Attitude towards skilled delivery service utilization**

Attitude will be measured by using five point Likert scale. Positive attitude will be scored by participants who respond above the mean of the attitude assessment questions and if below the mean they were categorized as having negative attitude

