Knowledge of danger signs during pregnancy has 14 items, Knowledge of danger signs of labor and childbirth has 9 items and knowledge of neonatal danger signs has 11 items. All Knowledge score will be computed by adding the total number of correct spontaneous responses to maximum number of items with a minimum score of 0 and maximum of number of items (0 when a mother mentioned none of the key danger signs and maximum number when the mother mentioned all the danger signs). Spontaneous response is respondents’ naming of danger signs without giving option of the respective signs. Accordingly, two categories will be developed for knowledge of danger signs (Good and poor categories). Women who mention at least three neonatal danger signs will be considered to have good knowledge whereas those who mentioned less than three of the danger signs will be labelled to have poor knowledge as stated by several studies. Questionnaire on BPCR is adopted and modified from monitoring BPCR tools for maternal and new-born health (Maternal, 2004). Attitude towards skilled delivery service utilization has 12 items that will be measured by using Likert scale where respondents are supposed to strongly agree, agree, neutral, disagree and strongly disagree. The overall attitude score will computed by summing up the items after performing the reverse scoring for negatively worded sentences. A higher composite score indicated a more favourable attitude.

*Perception of Pregnancy Risk Questionnaire (PPRQ****)*** was developed by Heaman and Gopton (Heaman and Gupton, 2009). It is a self-report questionnaire consisting of 9 visual analogue scales designed to measure a pregnant woman’s perception of her pregnancy risks. This questionnaire consists of two subscales that include four questions about the risk to self (mother), (for example “is a risk of having a cesarean section”); and five questions about risk to the baby, (for example “is a risk of baby having a birth defect”). “Respondents will be asked to put a vertical mark through the line to indicate their assessment of risk for each Item,” (yielding a score ranging from 0-100). A total PPRQ score will be obtained by adding the score for each of the 9 items, and then dividing by 9, to obtain a score out of 100. Higher scores will indicate higher levels of perceived risk.

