**Part VIII Attitude towards safe delivery utilization**

| 701 | Some people believe that any pregnant woman can develop delivery complication | 1. Strongly disagree; 2. Disagree; 3.Neutral; 4. Agree; 5. Strongly agree |  |
| --- | --- | --- | --- |
| 702 | Some people feel that delivery complications can be dangerous to the health of a woman | 1. Strongly disagree; 2. Disagree; 3.Neutral; 4. Agree; 5. Strongly agree |  |
| 703 | It is believed that delivery complications can‘t be dangerous to the health of the new born | 1. Strongly disagree; 2. Disagree; 3.Neutral; 4. Agree; 5. Strongly agree |  |
| 706 | According to some people‘s belief a woman should plan ahead of time where she will give birth to her baby. | 1. Strongly disagree; 2. Disagree; 3.Neutral; 4. Agree; 5. Strongly agree |  |
| 707 | Some women feel that they shouldn‘t plan ahead of time how they will get to the place where they will give birth. | 1. Strongly disagree; 2. Disagree; 3.Neutral; 4. Agree; 5. Strongly agree |  |
| 708 | Some women feel that every pregnant woman  need a skilled care at delivery | 1. Strongly disagree; 2. Disagree; 3.Neutral; 4. Agree; 5. Strongly agree |  |
| 709 | Few women feel that being attended by male  health personnel during delivery is unethical and shame | 1. Strongly disagree; 2. Disagree; 3.Neutral; 4. Agree; 5. Strongly agree |  |
| 710 | According to the feeling of some pregnant  women it is very shameful to deliver on  delivery bed in labor ward | 1. Strongly disagree; 2. Disagree; 3.Neutral; 4. Agree; 5. Strongly agree |  |
| 711 | Many women believe that women do not go to  a health facility for delivery, mainly because it is too expensive. | 1. Strongly disagree; 2. Disagree; 3.Neutral; 4. Agree; 5. Strongly agree |  |
| 712 | Many women believe that women do not go to  a health facility for delivery because health personnel do not treat them respectfully  . | 1. Strongly disagree; 2. Disagree; 3.Neutral; 4. Agree; 5. Strongly agree |  |

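### Attitude is split at a mean the protocol does not identify, so reported levels can depend on the intervention effect; separately, 12 attitude items are stated but both forms carry 10

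*Protocol*

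**What the plan says.** Section 4.16 of the protocol (Measurements and indicators) describes a summed Likert score, with negatively worded items reversed before summing: "Attitude towards skilled delivery service utilization has 12 items that will be measured by using Likert scale", and "A higher composite score indicated a more favourable attitude".

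The later operational definition of attitude turns this into two groups. For the favourable group it reads "Positive attitude will be scored by participants who respond above the mean of the attitude assessment questions". For the remaining women the rule is "if below the mean they were categorized as having negative attitude". It does not identify the mean, and it gives no group to a woman who scores exactly at it.

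In Annex 1, Part VIII, the item on danger to the new-born (703, "It is believed that delivery complications can‘t be dangerous to the health of the new born") is followed directly by 706 ("According to some people‘s belief a woman should plan ahead of time where she will give birth to her baby"). The Amharic form has the same gap.

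On the role of attitude:
- The conceptual framework lists it among the expected psychosocial changes.
- The summary names it among the data from the repeated household surveys, shortly before it plans a logistic GEE for the intervention effect.
- Section 4.7 lists it as a behavioural independent variable. The dependent variables there are ANC and skilled delivery only.
- It does not appear in the specific objectives (3.2) or among the major outcome variables in the summary table of study design.

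Section 4.19 says the two surveys are combined and that each model is fitted with a period-by-allocation interaction.

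**The concern.** A cut taken from the data has no fixed meaning. If end-line answers from the intervention arm enter the mean, a successful intervention raises the threshold that control women have to pass. The percentage positive in each arm, and possibly its change over time, then reflects the choice of mean as well as women's attitudes. The protocol leaves that choice open, so the same answers could be reported in materially different ways.

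The split also discards information that the summed score in 4.16 already holds.

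The item count is a second and independent matter. A reader who relies on 4.16 would take the score range, or any midpoint, from the wrong number of items.

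**Working it through.** **Item count.** The numbers 701 to 712 span 712 - 701 + 1 = 12, which matches the stated figure. The items printed are 701-703 (3) and 706-712 (7), so 10 in each language. With five response levels the sum runs from 10 × 1 = 10 to 10 × 5 = 50 (midpoint 30). Twelve items would give 12 to 60 (midpoint 36).

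**Cut-off.** From the protocol: two arms allocated 1:1, and two surveys (baseline and end line). Assumed, because the protocol gives no values: normal scores with SD 1, equal arm sizes, both arms at mean 0 at baseline, control still at 0 at end line, and the intervention arm shifted to d = 0.2, 0.5 or 0.8 SD.

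Percent positive in a group is Φ(group mean - cut). The cuts are:
- Mean of each survey: 0 at baseline, (0 + d)/2 = d/2 at end line.
- One mean over both surveys: (0 + 0 + 0 + d)/4 = d/4 at both times.
- Baseline mean, fixed: 0 at both times.

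For example, at d = 0.5 control at end line is Φ(-0.25) = 40.1%, Φ(-0.125) = 45.0% and Φ(0) = 50.0% respectively.

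| d (SD) | Mean used | Control, baseline → end | Intervention, baseline → end | Difference in change (points) |
|---|---|---|---|---|
| 0.2 | each survey | 50.0 → 46.0 | 50.0 → 54.0 | 8.0 |
| 0.2 | both surveys | 48.0 → 48.0 | 48.0 → 56.0 | 8.0 |
| 0.2 | baseline | 50.0 → 50.0 | 50.0 → 57.9 | 7.9 |
| 0.5 | each survey | 50.0 → 40.1 | 50.0 → 59.9 | 19.7 |
| 0.5 | both surveys | 45.0 → 45.0 | 45.0 → 64.6 | 19.6 |
| 0.5 | baseline | 50.0 → 50.0 | 50.0 → 69.1 | 19.1 |
| 0.8 | each survey | 50.0 → 34.5 | 50.0 → 65.5 | 31.1 |
| 0.8 | both surveys | 42.1 → 42.1 | 42.1 → 72.6 | 30.5 |
| 0.8 | baseline | 50.0 → 50.0 | 50.0 → 78.8 | 28.8 |

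(The last column comes from unrounded values.)

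The false fall in control under the first rule is 4.0, 9.9 and 15.5 points. Under the second rule there is none, but even the baseline percentages depend on an effect that has not yet occurred.

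On the odds-ratio scale of the planned logistic model, at d = 0.5:
- Each survey: (0.5987/0.4013)² = 2.23.
- Both surveys: (0.6462/0.3538)/(0.4503/0.5497) = 2.23.
- Baseline: 0.6915/0.3085 = 2.24.

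**Check with a discrete score.** A simulated sum of ten five-point items, with the shift applied to the underlying trait and the mean recalculated at each survey, gave control 47.6% → 42.3% at d = 0.5 and 52.3% → 37.6% at d = 0.8. At d = 0.2 there was no fall (47.4% → 47.5%), because the integer score is coarse. With one mean over both surveys, control stayed flat throughout.

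**Information.** For a small shift in a normal score, a split at the centre has efficiency 2/π = 0.637 relative to the score itself.

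**The case against.** The sponsor can say that the protocol never states that the mean is recalculated at each survey. Combining the surveys, as 4.19 plans, fits a single mean at least as well, and then control shows no decline. This stands. A reader might infer from the definition that the trial will show a false decline in the control arm, but the text does not support that; it is one of several possible readings. A reader might also connect the missing items with such a decline. The item count changes the score range and any midpoint, and it cannot move control women from one group to the other over time.

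It is also fair that one cut applies to both arms at each survey, so the period-by-arm contrast in 4.19 keeps its direction and nearly its size, and that attitude is neither a dependent variable nor a trial objective. Both points limit the consequence.

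Two further replies carry less weight. One is that the SAP could name the mean. The protocol, however, has already stated a rule, and that rule is incomplete. The other is that the annexed forms may change after the pre-test in 4.18, or that rows were lost when the text was read. The final instrument is indeed not known, but the same two numbers are absent in both languages, which makes accidental loss unlikely, and 4.16 must in any case agree with the form.

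The summed score remains available beside the category, so the lost information matters only if the split is what is analysed. The protocol does not say which will be.

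**Conclusion.** The point holds in a limited form. The cut is undefined and leaves ties unassigned, and any mean that includes end-line data ties it to the intervention effect. For assumed shifts of 0.2 to 0.8 SD, control would appear to fall by about 4 to 16 points if the mean is recalculated at each survey. If one mean serves both surveys, control would read about 2 to 8 points below 50% with no change over time. These figures rest on normal scores, equal arms and no true change in control; a coarse integer score can remove the smallest of them.

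The randomised contrast is almost untouched: at most 2.3 points between readings (31.1 against 28.8 at 0.8 SD). The cost to that contrast is precision, about 36% of the information for independent normal scores.

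The gap for ties is minor with a sample mean, which rarely falls exactly on an attainable score, but it matters if the cut is a whole number.

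The conflict between 12 and 10 items is certain on the face of the protocol and is a separate error. Neither part bears on skilled delivery, for which the trial is sized, or on ANC. This is a small, worthwhile correction to a secondary behavioural measure.

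**What to change.** - Replace the operational definition: analyse the summed score of 4.16 as a continuous variable in a model that adjusts for clustering, with the period-by-allocation term already planned in 4.19.
- If a category is also reported, fix one cut in advance at the baseline mean pooled over both arms, apply it at both surveys, and state to which group a score equal to the cut belongs.
- Correct the item count in 4.16 to 10 so that it matches the forms, and give the range as 10-50.

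The cost is a change of wording in two places and no new data. The small downside is that the effect is reported as a mean difference, which is less immediate than a proportion; the fixed-cut category can stand beside it. If items 704 and 705 were meant to be asked, restoring them is a larger change: both language versions must be revised and the extra items collected, at both surveys if the scores are to be comparable.

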## 4.19 Statistical analysis

Data of baseline and end-line surveys will be combined and analyzed using Stata 14.1. Analyses will be based on the intention-to-treat principle and compared differences of the outcomes between the intervention and control at both individual and cluster levels. First, Univariate analyses will be performed to explore the characteristics of respondents. We then will use logistic regression with random effects to estimate the effect of the intervention on prenatal behaviour, adjusting for clustering. Generalized estimated equations (GEE) regression analyses adjusted for clustering will be used to test the effect of the intervention on promoting maternal health behaviour. We will repeat analyses for the primary and secondary outcomes adjusted for baseline differences by fitting an interaction term between study period (baseline vs intervention) and allocation in each model. Mixed-effects multilevel logistic regression model will be used to identify determinants of birth preparedness and complication readiness.

**For qualitative study:** The interviews will be recorded and transcribed verbatim. The transcripts will be thematically analyzed using the qualitative software program Atlas.ti 6.0. Two analysts will independently code the transcripts and subsequently review, discuss, and refine the coding schemes until consensus will be reached. Emerging concepts will be assessed using the constant comparative method from grounded theory. This means that when this concept will be identified, previously analyzed interviews will be reviewed in order to check if their content fitted into this concept. A final version of the code book will be then developed leading to identification of themes, and sub-themes. Coded transcripts will be further analyzed and summarized in narratives for each theme and sub-theme. Study findings will be presented, discussed, and validated in a stakeholder meetings conducted in regional and district health offices.

| S.no | Research objectives | Study populations | Study design | Data source | Major outcome variables | Analytic model |
| --- | --- | --- | --- | --- | --- | --- |
| 1 | To assess effectiveness of trained religious leaders’ engagement in maternal health education on knowledge of danger signs during pregnancy and child birth | Pregnant mothers | Cluster randomized control trial | Household survey | knowledge of danger signs during pregnancy and child birth | Generalized estimated equations (GEE) regression analyses |
| 2 | To assess effectiveness of trained religious leaders’ engagement in maternal health education on antenatal care service utilization | Pregnant mothers | Cluster randomized control trial | Household survey | antenatal care service utilization | Generalized estimated equations (GEE) regression analyses |
| 3 | To assess effectiveness of trained religious leaders’ engagement in maternal health education on skilled delivery service utilization | Pregnant mothers | Cluster randomized control trial | Household survey | skilled delivery service utilization | Generalized estimated equations (GEE) regression analyses |
| 4 | To develop and validate religious’ leaders maternal health education engagement scale: elicitation study on mothers’ perception on religious leaders based maternal health education then scale development | Pregnant mothers | Cross-sectional study | Household survey | Religious leaders engagement in maternal health education | exploratory factor analysis |
| 5 | To explore role of religious leaders in promoting maternal and child health: a religious leaders’ view in rural setting of Hadiya Zone, Southern Ethiopia.  **Research questions:**   1. Do religious leaders address the topic of maternal health in their contacts with members of their congregations? If so, when and how do they address the topic? 2. To what extent religious leaders willing to enter into a dialogue with authorities on the topic of maternal health? | Religious leaders | Grounded theory | In-depth interviews and FGDs among religious leaders | NA | Thematic analysis |

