## 4.8 Sample size

In accordance with the main objective of the larger study, the sample size estimate is designed to detect changes in the proportion of skilled delivery service utilization. The sample size is calculated using stata software based on the following assumptions. Tail (s): One; effect size (d): 0.15; **α** error probability = 0.05; power (1-**β** error probability) = 0.8, and allocation ratio (N1/N2) = 1. This gives a sample size of 155. Then, adding design effect, DE = 1+(m-1)ICC , where m=Average cluster size, m= 50, ICC=0.02 based on a published study ICC (Killip et al., 2004), DE=2, and allowing for a 10% loss to follow up, the total sample size is 682 (N1 = 341 and N2 = 341). N1 and N2 are sample sizes in the control and intervention group, respectively. Based on these assumptions, the estimated sample size is: 306 pregnant mothers per group to detect a 15-percentage point anticipated difference in the proportion of skilled delivery service utilization (an increase from 26% to 41%). This estimate is based on the baseline skilled delivery service utilization in the Ethiopia Demographic and Health Survey (26% from EDHS 2016, SNNP region report) in the control group (CSA, 2016).

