## Randomization

There are a total of 12 clusters for this cluster randomized trial. The researcher and kebele leaders, religious leaders and HEWs will conduct the randomization to produce comparable groups and eliminate the source of selection bias in the assignment of kebeles to the intervention and control groups. Simple randomization with a 1:1 allocation will be applied to assign clusters to either control or intervention groups. First, 12 nonadjacent clusters will be selected by a lottery method. Then, the 12 clusters were listed alphabetically. A list of random numbers will be generated in MS Excel 2010 and the generated values will be fixed by copying them as “values” next to the alphabetic list of the clusters. These are arranged in ascending order according to the generated random number. Finally, the first 6 clusters will be selected as intervention clusters and the last 6 as control clusters. A statistician that will be blinded to study groups and not participated in the trial will do the generation of the allocation sequence and the randomization of clusters (Figure below). The intervention group is assigned to receive training from religious leaders on maternal and neonatal health and the control group will be left to continue the current practices.

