## 4.11 Trial design

This study is a parallel two-arm a cluster randomized controlled trial with 8 clusters. The trial arms are as follows: 1) religious leader training and 2) standard cares. The kebeles health posts are designated as clusters for the trial. Outcome assessments will be made using repeat cross-sectional surveys at baseline (prior to intervention roll-out) and at 4 months post intervention (i.e. the end line). A schematic for the trial design is displayed in Figure 2.

Screening

Two districts out of 13 districts of Hadiya Zone selected purposely

Non-adjacent 12 kebeles from two districts selected randomly

Randomization

Cluster randomization of 12 clusters to 2 study groups

Intervention groups: (6 clusters)

Control groups: (6 clusters)

Recruitment

-Recruit pregnant mothers with gestational age less than 20 wks. (n =341)

- Baseline data collection

base line data collection

**-**Recruit pregnant with mothers with gestational age less than 20 wks. (n =341)

-Baseline data collection

Intervention

Training for pregnant mothers by trained religious leaders

The usual care only

End line

End line data collection

End line data collection

Figure 2: Diagrammatic representation of the randomization of study cluster (kebeles)

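### GEE is the named test for objectives 1 to 3 with 12 clusters and no small-sample method; run in the usual way, its two-sided error is about 9 to 10% rather than 5%

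*Protocol*

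**What the plan says.** Section 4.19 gives the test: "Generalized estimated equations (GEE) regression analyses adjusted for clustering will be used to test the effect of the intervention". The preceding sentence names a second model: "We then will use logistic regression with random effects to estimate the effect of the intervention on prenatal behaviour, adjusting for clustering". The Summary also says that the effect will be assessed with GEE, and the study design summary table gives GEE as the only analytic model for objectives 1 to 3, which are the three randomised objectives. Section 4.19 further promises a comparison at cluster level, without a method, and a repeat analysis with an interaction between study period and allocation.

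On the number of clusters, the Randomization section says "There are a total of 12 clusters for this cluster randomized trial" and that "the first 6 clusters will be selected as intervention clusters and the last 6 as control clusters". Section 4.11 says "This study is a parallel two-arm a cluster randomized controlled trial with 8 clusters", while its own flow diagram shows 12.

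Section 4.8 sizes the trial for "an increase from 26% to 41"%, with "error probability = 0.05", "error probability) = 0.8, and allocation ratio (N1/N2) = 1", one tail, an ICC of 0.02 and an average cluster size of 50. It arrives at 155, then 306 per group, then 341 with loss to follow-up. Nowhere is there a bias-corrected variance, a t or F reference based on clusters, or a permutation test.

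**The concern.** The robust variance used with GEE is justified when there are many clusters. With six per arm it is biased low, because residuals are taken around arm means estimated from the same six clusters. Comparing the resulting statistic with a normal distribution also ignores that the variance is estimated on only about 10 degrees of freedom. Both faults act in the same direction: p-values are too small and confidence intervals too narrow.

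This would affect all three randomised objectives, and section 4.20 plans scale-up on the strength of the results. It also bears on the design, because the power in section 4.8 makes no allowance for the small number of clusters.

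**Working it through.** **1. The plan's own sample size.** Inputs from section 4.8: 26% and 41%, alpha 0.05, power 0.80. The two-proportion formula without continuity correction, with mean proportion 0.335, is

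n = [z(alpha) × sqrt(2 × 0.335 × 0.665) + 0.842 × sqrt(0.26 × 0.74 + 0.41 × 0.59)]² / 0.15².

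- Two-sided (z = 1.96): 154.2, rounded up to 155, the stated figure.
- One-sided (z = 1.645): 121.4, rounded up to 122.

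So 155 is a two-sided figure although the text says one tail. The design effect is 1 + 49 × 0.02 = 1.98, and 155 × 1.98 = 306.9 (stated 306). Then 155 × 2 × 1.10 = 341. All these steps use normal quantiles.

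**2. Error of the uncorrected test, closed form.** Take equal cluster sizes and treat cluster results as approximately normal. The uncorrected sandwich variance divides by 6 within each arm where an unbiased one divides by 5. The Wald statistic is then t(10) × sqrt(6/5) = t(10) × 1.095. The factor n/(n−1) = 12/11, which some software applies, reduces the multiplier to sqrt(1.2 × 11/12) = 1.049.

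| Variance, normal reference, 12 clusters | Two-sided 5% | One-sided 5% |
|---|---|---|
| Uncorrected sandwich | P(abs t10 > 1.96/1.095) = 10.4% | P(t10 > 1.645/1.095) = 8.2% |
| With 12/11 factor | P(abs t10 > 1.96/1.049) = 9.1% | P(t10 > 1.645/1.049) = 7.4% |
| Unbiased variance | P(abs t10 > 1.96) = 7.8% | P(t10 > 1.645) = 6.5% |

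With 8 clusters the uncorrected two-sided figure is P(abs t6 > 1.96/1.155) = 14.1%.

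**3. Simulation under the null.** Beta-binomial data, outcome proportion 0.26, 12 clusters of 51 (306/6), uncorrected sandwich with z = 1.96, two-sided:

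- ICC 0.02: 10.3%. Over ICC 0.005 to 0.10: 10.25 to 10.5%.
- Cluster sizes proportional to the kebele populations in Table 1: 10.5%.
- One-sided 5% at ICC 0.02: 8.1%.

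The inflation therefore hardly depends on the assumed ICC. Full GEE fits with exchangeable correlation (1,600 replicates per scenario, Monte Carlo standard error about 0.75 percentage points) gave 8.8 to 10.6% at end line and 10.1 to 11.5% for the period-by-allocation interaction. Model-based standard errors did not help: 8.6 to 10.1% at end line and 6.9 to 15.2% for the interaction.

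**4. Error after correction.** A leverage-corrected (Kauermann-Carroll type) variance with t on 10 df gave 4.9 to 5.1% over the same ICC range and with unequal sizes.

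**5. Power of a valid test at 306 per arm.** With clusters of 51 the design effect is 1 + 50 × 0.02 = 2.00. The standard error is sqrt(2.00 × 0.4343 / 306) = 0.0533, where 0.4343 = 0.26 × 0.74 + 0.41 × 0.59. The noncentrality is 0.15/0.0533 = 2.815.

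- Normal reference: 80.4%, which matches the plan.
- t on 10 df, two-sided (critical value 2.228): 71.9%. Simulation of the corrected GEE test gives 70.4%.
- t on 9 df, if district is added (critical value 2.262): 70.8%.
- t on 10 df, one-sided 5% (critical value 1.812): about 83%.

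On the same two-sided basis with arm only, 14 clusters of 51 give 79.7% and 16 give 85.6%.

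**The case against.** The strongest reply is that the protocol never states the faulty step. Section 4.19 names no variance estimator, reference distribution or degrees of freedom. Such details often sit in a statistical analysis plan, and GEE with 12 clusters is valid once corrected. This stands as a limit on the claim. A reader might infer that the protocol commits to an invalid test or that the error rate is certain to double; the text does not support that, because it is silent on a correction and does not rule one out. What remains is that the protocol itself fixes both the test and six clusters per arm, and the usual execution of that pair has the wrong error rate. The loss of power also follows from the protocol's own figures and cannot be repaired by later analysis wording.

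Doubling is also a two-sided statement. Under the one tail of section 4.8 the inflation is about 1.5 to 1.6 times. Under a two-sided test, half of the false positives would favour control.

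A reader might further infer from section 4.19 that the reported estimate will come from the random-effects model and the p-value from GEE. No sentence pairs them, and the Summary and the summary table point to GEE as the lead model. The gap would be small in any case: at ICC 0.02 and 26% the between-cluster variance on the logit scale is about 0.02/(0.26 × 0.74) = 0.10, and the two log odds ratios differ by about 2%.

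Finally, the promised cluster-level comparison could be a valid test. It has no method and is not named as the test, so it does not settle the matter.

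**Conclusion.** The concern holds in conditional form. The protocol names GEE as the test for objectives 1 to 3 with six clusters per arm and no small-sample method. Run with a robust variance and a normal reference, its nominal 5% error is about 9 to 10% two-sided, or about 7 to 8% one-sided.

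These figures rest on no correction beyond, at most, the n/(n−1) factor, and on 12 clusters analysed. They change little over ICC 0.005 to 0.10 or with the unequal kebele sizes of Table 1. If section 4.11 were right about 8 clusters, the uncorrected two-sided error would be about 13 to 14%.

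Under the plan's own rates, ICC and 306 per arm, a valid two-sided test has about 70 to 72% power rather than 80%.

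**What to change.** In section 4.19:

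- Name one primary analysis. Either use GEE logistic regression with kebele as the cluster, a small-sample corrected variance (for example Kauermann-Carroll) and a t reference with df equal to clusters minus cluster-level parameters (10 with arm only, 9 with arm and district), or use a cluster-level t test on kebele proportions.
- Take the estimate, confidence interval and p-value from that one model, and keep the random-effects logistic model as a sensitivity analysis.
- Apply the same small-sample correction to the period-by-allocation analysis.
- State whether the test is one- or two-sided, in agreement with section 4.8, where the text says one tail but 155 is a two-sided figure.

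In section 4.11, reconcile the 8 clusters with the 12 given elsewhere. In section 4.8, restate power for the test actually chosen.

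The wording and code cost little. The real cost is power: about 70 to 72% two-sided at 306 per arm. The sponsor can accept and report that, or add clusters if recruitment still allows; about 14 clusters of 51 restore roughly 80% on the plan's assumptions.
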